### Trial interventions

The trial will use a 2 by 2 factorial design to test not only whether glutamine and selenium on their own are effective, but also whether there is extra effectiveness from the combination.

For this reason allocation will be to one of four groups, see table 1.

**Table 1 T1:** The trial will use a 2 by 2 factorial design to test not only whether glutamine and selenium on their own are effective, but also whether there is extra effectiveness from the combination. For this reason allocation will be to one of four groups.

	**No glutamine**	**Glutamine**
**No additional selenium**	Standard PN bag 12.5 g nitrogen, 2000 kcal daily	PN bag, 12.5 g nitrogen (including 20.2 g glutamine), 2000 kcal daily
**Additional selenium**	Standard PN bag 12.5 g nitrogen, 2000 kcal daily 500 μg selenium daily	PN bag, 12.5 g nitrogen (including 20.2 g glutamine), 2000 kcal daily 500 μg selenium daily

All formulated PN bags (1500 ml volume) are isonitrogenous and isocaloric and have been tested for long-term stability by Fresenius-Kabi. Standard additions of fluid, electrolytes, vitamins and minerals will be allowed (including standard doses of selenium). dditional nitrogen and/or energy will not however, be allowed in the PN (to retain the isonitrogenous nature of the interventions). Supplementation will be given for seven days only (on ICU and subsequent wards and hospitals if practicable).

Once the decision is made to commence PN, it is desirable that SIGNET PN is given from the start. If this is not possible SIGNET PN should be started within 48 hours of commencing PN on ITU or HDU. If SIGNET PN is discontinued for any reason, e.g. line removed, SIGNET PN can be restarted within 48 hours from discontinuation and a total of 7 days of SIGNET PN may be given. Patients who have been given PN outside of critical care are eligible for recruitment. A patient may be recruited to the trial only if the pharmacy has sufficient stock for 5 days of bags of PN at the start of therapy.

The volume of feed may be reduced for men under 60 kg in weight and women under 70 kg. Consultants on intensive care may opt not to enter patients into the trial if they perceive the patient either to be at risk of refeeding syndrome, or to require a gradually phased introduction of nutrition support.

Patients entered in the trial will be monitored as is standard practice in the ICU.

### Treatment allocation

The existing central randomisation service (fully automated computerised telephone randomisation) in the Health Services Research Unit at the University of Aberdeen will be used to randomise patients. Recruiting staff will telephone the randomisation line and will be asked to key in details of identification and important prognostic factors (see below), when confirming eligibility and consent. Consent procedures will adhere to the 2003 Mental Health (Care and Treatment) (Scotland) Act. Random allocation to one of the four possible treatment combinations (see above) will be minimised on trial centre; age (<65 years or ≥ 65 years); sex; patient groups (medical or surgical (including trauma)); and, patient nutritional status (under-nourished, normal or obese – subjective clinical assessment [24]. A four digit number for that patient will be provided by the automated randomisation service, the research nurse accessing the randomisation service will then inform the centre pharmacy of this randomisation number. The trial office, based at the University of Aberdeen will have provided each pharmacy with a list of these random numbers linked to one of the four treatment allocations, thus maintaining the blinding of local investigators to the trial treatment. Figure 1 summarises these arrangements.

**Figure 1 F1:**
[figure not shown]
**Trial Flowsheet**. Randomised trial of glutamine and selenium supplemented parenteral nutrition for critically ill patients.

#### Subsequent arrangements

##### Informing key people

Following formal trial entry, the Trial Office or local research nurse will also contact:

• the ***consultant and ward staff ***caring for the patient on discharge from the intensive care unit – informing them of participation in the trial and the possible continuation of trial treatment.

• the ***general practitioner ***– informing the GP practice of participation in the trial and the (few) implications for the practice. This letter includes a brief description of the trial together with a request that the general practitioner notifies the Trial Office if the patient dies.

• the ***'best contact' ***asking for assistance to complete the questionnaires (see below)

### Additional information sought by post at three and six months after entry

Questionnaires will be sent to participants by post at three and six months post randomisation, which will contain:

i) The SF-12 questionnaire and the EQ-5D questionnaire

ii) Contacts with health services after discharge

A cost questionnaire will also be sent to participants by post at 6 months to elicit

(i) Costs to patients and carers (travel costs, time spent travelling and attending appointments, time lost from usual activities)

Participants will be sent up to two reminders by post if the questionnaires are not returned to the Trial Office.

If it is known that a participant is still in hospital at three and six months, questionnaires will not be sent to their home address. Instead the trial office will ask the study nurse or the staff looking after the participant to assist the participant in completing the questionnaires, if appropriate.

### Notifications by general practitioners

A letter and information sheet will ask the general practitioner to notify the Trial Office by telephone if the participant dies (and to give cause of death).

### Notifications by 'best contact'

A brief letter and freepost envelope will be sent to the 'best contact' (relative that gave assent) at the time of the participant's hospital discharge. The letter will ask if he/she could assist the participant to complete the three and six month questionnaires if this is appropriate.

#### If the Trial Office fails to make contact

The Trial Office will liaise with the local study nurse if there is ever failure of contact with a participant. In these circumstances the nurse or Trial Office will telephone the general practitioner's (GP's) surgery to check vital status 24–48 hours before telephoning the participant. If the GP refuses to disclose this information, the patient will not be contacted.

#### Routine data collection

Information on subsequent hospital admissions and deaths will be collected by registration with the Information and Statistics Division Scotland (ISD) and the National Office of Statistics (ONS) and NHS Central registers

### Data collection and processing

Data from the various sources outlined above will be sent to the Trial Office in the University of Aberdeen for processing. Staff in Aberdeen will work closely with study nurses to secure as complete and accurate data as possible. A random 10% sample of data will be double entered to check accuracy. Extensive range and consistency checks will further enhance the quality of the data.

### Analysis plans

#### Ground rules for the statistical analyses

The statistical analyses will be based on all people randomised, irrespective of subsequent compliance with nutritional support. The principal comparisons will be:

(i) all those randomised glutamine versus all those not allocated glutamine

(ii) all those randomised selenium versus all those not allocated selenium

(iii) all randomised glutamine and selenium versus all randomised glutamine alone versus all randomised selenium alone versus all randomised placebo

Evidence will be sought for an interaction between glutamine and selenium.

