### Power calculation

The primary endpoint for the trial is the proportion of patients acquiring infection(s) after starting trial PN. Systematic reviews indicate that the reduction in proportion of patients acquiring infections in previous trials ranged from approximately 50% in the control arm to 40% in the intervention arm. Removing Griffiths' glutamine trial [31,32] – which only reported infections in a post-hoc analysis – shows the effect may indeed be greater (from 50% in the control arm to 30% in the intervention arm). A plausible reduction to detect would be the midpoint of these two estimates (i.e. a reduction from 50% to 35%), hence 340 participants would be required to detect this size of difference (with 80% power and 2p < 0.05) [33].

Given the high mortality rates in critical care patients [1], we have allowed for potential loss of patients to follow-up over the six months (see below – this would primarily affect secondary outcomes such as quality of life measures). We have consequently inflated the sample size requirement by approximately 20%, thus plan to recruit 500 patients to the trial.

Based on routine data available from the Scottish Intensive Care Society (SICS) audit database, the average length of ICU stay for patients receiving PN is approximately 9 (SD 7) days. For a 2 day reduction in ICU stay to be detected, with 80% power and 2p < 0.05, a trial of approximately 400 patients would be required. As we do not expect any dropout from the trial prior to discharge, we are adequately powered to detect this level of change.

A trial with 500 patients would allow us to detect a quarter of a standard deviation (0.25SD) change in hospital length of stay with 80% power and 5% significance (assuming all data for length of stay are available).

A trial of 340 patients would have 80% power and 5% significance to detect differences in Quality of Life measures of approximately 0.33SD (a third of a standard deviation change) or 90% power to detect a 0.5SD change. Previous research in the behavioural field suggests that a 0.5SD change is the level of change that should be associated with a moderate change in quality of life measures [34,35]. As such we are well powered to detect meaningful changes in quality of life measures.

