### Data analysis

Analysis of dichotomous outcomes will be analysed using statistical tests such the Chi-squared test. Continuous measures will be analysed using t-tests (with transformation of data to Normality if appropriate), or non-parametric equivalents. A further analysis accounting for the inter-relationship between deaths and length of stay will be undertaken, akin to that described for ventilator-free days by Rubenfield [26] mentioned earlier. This, for example, would allow the apparently short length of stays associated with early deaths to be accounted for appropriately. A significance level of 2p < 0.05 will be considered as evidence of statistical significance for the primary outcomes. Confidence intervals will also be presented where appropriate. The economic analysis will incorporate sensitivity analysis, and confidence intervals will be constructed around stochastic cost data using techniques such as bootstrapping [27].

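### Principal comparisons (i) and (ii) pool over the other supplement and only unstratified tests are named; stratifying by the other randomised factor would be a small, free gain in precision

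*Protocol article*

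**What the plan says.** Ground rules for the statistical analyses lists three principal comparisons. The first is "i) all those randomised glutamine versus all those not allocated glutamine" and the second is "ii) all those randomised selenium versus all those not allocated selenium". Each sets one half of the trial against the other half, whatever the patients received of the second supplement. The third, "iii) all randomised glutamine and selenium versus all randomised glutamine alone versus all randomised selenium alone versus all randomised placebo", keeps the four cells apart. The section closes with "Evidence will be sought for an interaction between glutamine and selenium", without naming a method.

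Data analysis gives the tests. For binary outcomes: "Analysis of dichotomous outcomes will be analysed using statistical tests such the Chi-squared test". For continuous outcomes: "Continuous measures will be analysed using t-tests (with transformation of data to Normality if appropriate), or non-parametric equivalents". The threshold is "A significance level of 2p < 0.05 will be considered as evidence of statistical significance for the primary outcomes". Neither section mentions stratifying by, or adjusting for, the other supplement.

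**The concern.** By design, about half of each group in comparisons (i) and (ii) also receives the other trial supplement. If that supplement works, each group mixes patients at two different underlying risks. A two-group test treats the gap between those risks as random variation. With balanced cells the gap cancels from the difference between the groups, so it does not belong in the error term.

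The result is a standard error a little larger than the design delivers and a test a little stricter than its nominal 5%. At stake is a small amount of power and confidence-interval width on the comparisons that carry the trial's conclusions. This is separate from adjusting for the minimisation factors: the omitted term is the trial's own second randomised treatment, known for every patient.

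**Working it through.** **Inputs.** From Power calculation: infection "a reduction from 50% to 35" per cent as the design effect; 50% to 30% as the larger effect; 50% to 40% as the smaller; ICU stay SD 7 with a 2-day effect; 340 required and 500 planned; 80% power, two-sided 5%. Assumed: four equal cells (Treatment allocation gives no ratio), and an effect of the other supplement between 0 and 20 points, since no infection effect is stated for each supplement separately.

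**The plan's own figure.** For two unstratified groups,
n per group = [1.960·√(2·0.425·0.575) + 0.842·√(0.50·0.50 + 0.35·0.65)]² / 0.15² = (1.370 + 0.582)² / 0.0225 ≈ 169.3, rounded up to 170, so 340 in total. This matches the protocol. The sample size was therefore set for an unadjusted two-group comparison.

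**Variance, binary outcome.** Take the tested supplement as null and let the other shift risk from p₀ to p₁. The pooled variance per patient is p̄(1−p̄). The variance that belongs in the comparison is the mean of p₀(1−p₀) and p₁(1−p₁). They differ by ((p₀−p₁)/2)².
- 50% to 35%: pooled 0.425·0.575 = 0.24438; within cells (0.2500 + 0.2275)/2 = 0.23875; ratio 1.024, an excess of 2.4%. The true two-sided error is that at z = 1.960·√1.0236 = 1.983, about 4.7%.
- 50% to 30%: pooled 0.240; within cells 0.230; ratio 1.043, an excess of 4.3%. True error about 4.5%.
- No effect: excess 0, error 5%.

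**Variance, continuous outcome.** With d the other supplement's effect in within-cell SDs, the ratio is 1 + d²/4. For ICU stay d = 2/7 = 0.286, so the ratio is 1.020: about 2% in variance, 1% in standard error.

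**Mortality, the other primary outcome.** As an illustration, take 30% hospital mortality and a relative risk of 0.75 for the other supplement (both figures appear in the Background), so 30% against 22.5%. Within cells (0.2100 + 0.1744)/2 = 0.1922; pooled 0.2625·0.7375 = 0.1936; excess about 0.7%.

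**Power at 500 (125 per cell).** Cells are ordered neither / tested only / other only / both.

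| Cells (% infected) | SE excess, pooled v stratified | Power, pooled v stratified |
|---|---|---|
| 50 / 35 / 35 / 20 (both 15 points) | 1.3% (0.0421 v 0.0416) | 94.5% v 94.8% |
| 50 / 35 / 35 / 24.5 (both relative risk 0.7) | 0.9% | 84.8% v 85.2% |
| 50 / 35 / 30 / 15 (tested 15, other 20) | 2.4% | 95.4% v 95.8% |
| 50 / 40 / 40 / 30 (both 10 points) | 0.5% | 62.8% v 63.2% |
| 50 / 40 / 30 / 20 (tested 10, other 20) | 2.3% | 65.6% v 67.2% (simulated) |
| 50 / 35 / 50 / 35 (other has no effect) | 0% | 92.6% v 92.6% |

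For the first row, pooled SE = √[(0.425·0.575 + 0.275·0.725)/250] = 0.0421, and stratified SE = ½·√[(0.2500 + 0.2275 + 0.2275 + 0.1600)/125] = 0.0416.

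**Odds-ratio scale.** With the first row's cells, the standard error of the log odds ratio is 0.191 unadjusted and 0.194 adjusted, so adjustment raises it. The estimate moves further from zero as well, and z goes from 3.50 to 3.54.

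**The case against.** The strongest reply is that nothing here is wrong. The Chi-squared test is given only as an example, and a Cochran-Mantel-Haenszel test would be consistent with the wording. The article condenses a fuller protocol, and an analysis plan not shown may already include both factors. The pooled comparison is unbiased under balance, its error rate is at or below 5%, and the 340 was calculated on the same unadjusted basis. At the design effect the loss is about 0.3 points of power. The 1.6-point case pairs the two ends of the range in Power calculation and is not a planned scenario. The selenium evidence cited in the Background concerns mortality, so a 15- or 20-point infection effect for selenium is an assumption.

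All of this stands, and it sets the size of the point. It does not remove it. The only tests named are unstratified, the t-test wording is less open than the Chi-squared wording, and a better analysis is available at no cost. Comparison (iii) is not affected, but a four-group test does not give a more precise estimate of either main effect.

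A reader might infer that all three principal comparisons are affected, that the protocol commits itself to a plain Chi-squared test, or that the standard error is too large on every scale. The documents do not support these readings: (iii) does not pool, the Chi-squared test is illustrative, no effect measure is fixed, and on the log odds ratio the adjusted standard error is the larger one.

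**Conclusion.** A minor efficiency point that holds for comparisons (i) and (ii), on the risk-difference or mean-difference scale, and only if the other supplement works. The pooled variance is then about 2.4% too large (other supplement 50% to 35%), 4.3% (50% to 30%) or about 2% (ICU stay), and the test's true error is about 4.5% to 4.7% for the two infection effects. At 500 patients the power lost is about 0.3 points with both supplements at 15 points and 1.6 points in the least favourable case computed. If the other supplement has no effect, nothing is lost.

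The result rests on roughly equal cells and on assumed effects of the other supplement. It should not be read as bias, as an inflated false-positive rate or as an underpowered trial: the pooled test errs on the cautious side and no stated sample size changes.

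**What to change.** In Ground rules for the statistical analyses and in Data analysis, state that comparison (i) is stratified by or adjusted for selenium allocation and comparison (ii) for glutamine allocation:
- binary outcomes: a Cochran-Mantel-Haenszel test with a stratified risk difference or risk ratio;
- continuous outcomes: two-way analysis of variance in place of the t-test;
- rank-based analyses: a van Elteren test.

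Take the main effects from the model with both factors. Adding the product term to that model gives the interaction the protocol says it will look for. The cost is a sentence in the analysis text, with no new data and no extra patients. If the full analysis plan already does this, only the article's wording needs to be aligned.

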#### Measures of outcome

##### Primary

• Mortality – on ICU and HDU and overall at six months

• Infections – counted as participants with new reported infections and Centres for Disease Control (CDC) confirmed infections in the first 14 days [25].

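### The trial is sized on one primary endpoint (infection), yet two to four primary outcomes are listed and tested at an unadjusted 2p<0.05, with no power stated for mortality

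*Protocol article*

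**What the plan says.** Five places in the protocol article bear on this.

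- **Power calculation:** "The primary endpoint for the trial is the proportion of patients acquiring infection(s) after starting trial PN". The endpoint is singular. The section does not say whether infection means reported or CDC-confirmed, and it gives no time window.
- **Measures of outcome, Primary:** there are two bullets. Mortality is taken "on ICU and HDU and overall at six months". Infections are "counted as participants with new reported infections and Centres for Disease Control (CDC) confirmed infections in the first 14 days".
- **Abstract, Methods/design:** primary outcomes, in the plural, are infection and mortality, with infection counted as episodes over 14 days.
- **Ground rules for the statistical analyses:** the first principal comparison is "all those randomised glutamine versus all those not allocated glutamine". The second is the same contrast for selenium, and the third compares all four groups.
- **Data analysis:** "A significance level of 2p < 0.05 will be considered as evidence of statistical significance for the primary outcomes".

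A stricter level, 2p<0.01, is set only for subgroup analyses. The Power calculation gives power for infection, ICU stay, hospital stay and quality of life. It gives none for mortality.

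**The concern.** The article does not settle which outcome carries the trial's conclusion. One section has a single sized endpoint, while two others have several primary outcomes. The stated significance rule covers all of them equally. Two things are at stake.

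- **False positives.** If several primary outcomes are each tested at 5% within one treatment comparison, the chance that at least one is significant by luck is above 5%.
- **Interpretation of mortality.** A non-significant mortality result would carry the weight of a primary outcome, although the trial was not sized for it and the reader is not told what difference it could detect.

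The infection outcome also has competing definitions (episodes or participants, reported or CDC-confirmed). The endpoint that was sized therefore cannot be matched with certainty to one in the list.

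**Working it through.** **1. The plan's own figure.** Inputs from the Power calculation are 50% against 35%, 80% power and two-sided 0.05. The formula, with pooled variance under the null and no continuity correction, is

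n per group = [1.96·√(2·p̄·(1−p̄)) + 0.8416·√(p1(1−p1)+p2(1−p2))]² / (p1−p2)²

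With p̄ = 0.425: [1.96·√0.48875 + 0.8416·√0.4775]² / 0.0225 = 169.3, so 170 per margin and **340** in total. The stated figure reproduces. With 500 patients (250 per margin, assuming equal allocation) infection power is 92.6%.

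**2. How many primary outcomes.**

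- Two, if counted by domain (mortality, infection).
- Three, if mortality at its two times is separate and infection is one definition.
- Four, if reported and CDC-confirmed infections are also separate.

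**3. False-positive chance within one factorial margin.** For k independent tests at 0.05 the chance of at least one false positive is 1 − 0.95^k.

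- k = 2: 1 − 0.9025 = 9.75%
- k = 3: 1 − 0.857375 = 14.3%
- k = 4: 1 − 0.814506 = 18.5%

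These are ceilings. ICU and HDU deaths are almost entirely contained in six-month deaths, and the two infection counts presumably overlap. A simulation of four correlated null test statistics gave 14.7% to 16.7%. It assumed correlations of 0.6 to 0.8 within each domain and 0.1 to 0.2 between domains. Perfect correlation would give 5%. The four-group comparison is not counted here.

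**4. Mortality power.** Inputs are as follows.

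- 250 against 250 patients, two-sided 0.05.
- Control rates of 15% to 20% (ICU) and 30% (hospital) from the Background. These are general UK figures, used here as assumptions.
- 40% for six months, which is purely an assumption because the article gives no six-month rate.
- Relative risks from Systematic reviews: 0.75 is quoted for parenteral glutamine and for selenium in general intensive care; 0.71, 0.79 and 0.59 also appear.

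Power = Φ{[(p1−p2)·√250 − 1.96·√(2·p̄·(1−p̄))] / √(p1(1−p1)+p2(1−p2))}

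Example, 30% against 22.5%: (0.075·15.811 − 1.96·√0.38719) / √0.384375 = −0.054, and Φ(−0.054) = 48%.

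| Control mortality | RR 0.71 | RR 0.75 | RR 0.79 | RR 0.59 |
|---|---|---|---|---|
| 15% | 31% | 24% | 18% | 57% |
| 20% | 41% | 31% | 23% | 71% |
| 30% | 61% | 48% | 36% | 90% |
| 40% (assumed) | 78% | 65% | 50% | 98% |

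At 30% control mortality, 80% power needs a fall of about 10.8 points, to 19.2% (RR 0.64). At RR 0.75 it needs 1,080 patients.

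**5. What the alternatives cost in infection power.** Testing infection at 0.025 within a factor gives (0.15·15.811 − 2.2414·√0.48875) / √0.4775 = 1.165, or 87.8% with 500 patients. Hochberg across two outcomes rejects for infection whenever its p-value is at or below 0.025, and in some further cases, so 87.8% is a lower bound.

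**The case against.** The strongest reply is that this is a condensed article. Ranking of outcomes, alpha allocation and a success rule are commonly left to an analysis plan, which is not shown. Their absence alone is indeed no finding. What stands is that the article itself says one primary endpoint in one place and several in others, and fixes a significance level for the plural.

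A reader might also infer more than the text supports.

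- **At least four primary outcomes.** Four is the highest reading of the list, not a floor. There are two bullets, and the infection bullet can be one definition.
- **A false-positive chance of about 34%.** That is 1 − 0.95^8, four independent outcomes over both factors. Testing each factorial margin at 0.05 is accepted practice and is kept in the fix below, so the fair count is per factor.
- **A positive trial may be claimed from any one outcome.** No section states a success rule. Data analysis says only what counts as statistically significant.
- **Mortality is far underpowered.** This holds for RR 0.71 to 0.79 at 15% to 30% control mortality (18% to 61%). It is not established for six months, where no rate is given, and RR 0.59 gives 90% at 30%.

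The article claims definitive power only for infection, and keeping mortality primary is a legitimate choice. The sized infection conclusion is not endangered, since its power at 500 patients is 92.6%.

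**Conclusion.** The point holds as an inconsistency in stated text and should be fixed. One sized primary endpoint conflicts with a list of two to four primary outcomes, with infection defined in more than one way and a single unadjusted level for all.

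Followed as written, the false-positive chance within each factor is above 5%. It is bounded by 9.75%, 14.3% or 18.5% according to the number of outcomes, and is lower to the extent that they overlap. Mortality is primary with no stated power. At RR 0.75 that power is 24% to 31% at 15% to 20% control mortality, 48% at 30%, and about 65% at an assumed 40%.

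These results assume equal allocation. The mortality figures also rest on general UK rates, which may not match patients on parenteral nutrition.

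**What to change.** Reconcile the Abstract, Measures of outcome, Power calculation and Data analysis. The preferred form is:

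- **Sole primary:** participants with at least one new infection in the first 14 days, stating whether reported or CDC-confirmed, tested at 2p<0.05 for each of the two marginal comparisons.
- **Key secondary:** six-month mortality, with an effect estimate, 95% confidence interval and its power.
- **Secondary:** ICU and HDU mortality, and the infection definition not chosen as primary.

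Alternatively, keep six-month mortality co-primary and apply Hochberg across infection and six-month mortality within each factor. Infection power at 500 patients then stays at about 88% or more.

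The decision should be made before those who take it see any unblinded comparison. The study statistician supplies the confidential interim analyses, so should not be the one to choose.

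No extra patients or data are needed. The cost is a protocol amendment during recruitment, with more than 285 of 500 patients already entered. In addition, either mortality loses its primary status or infection power falls slightly, from 92.6% to no lower than 87.8%.
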